### Sample size

The sample size calculation is based on an expected small between-group effect size (Cohen’s *d* = 0.32) [45]. The calculation is conducted by the software program Power Analysis and Sample Size (PASS, 2008). The primary analysis will concern the hypothesis that the average post-intervention level of eating pathology in the waiting list control condition is higher than the average level of eating pathology in the three active intervention conditions. Assuming an alpha of 0.05 and a power of 0.80 (β-1) in a one-way ANOVA study, we need sample sizes of 79 participants in each of the four groups whose means are to be compared using a planned comparison. Taking into account a baseline variable (e.g., T0 assessment) for which we assume a Pearson correlation of 0.5 with the outcome variable, and thus explaining 25% of the variance of the outcome variable, the sample size per group can be reduced by 25% and is thus calculated as 0.75 × 79 = 60 per group. In order to account for dropout, recently reviewed to be approximately 30% for Internet-based interventions [46], the definitive number of participants we will need to recruit is 10/7 × 60 = 86 participants per group, resulting in 344 in total.

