### Statistical analyses

All statistical analyses will be performed in SPSS version 19. A two-tailed significance level of *α* = 0.05 will be used throughout the analyses. Both intent-to-treat and completers analyses will be conducted. Intent-to-treat analyses will include every participant who is randomly allocated to the intervention, regardless of withdrawal or deviation from the protocol [47]. Someone will be considered a completer in case he/she has completed both T0 and T1 assessments, and at least five monitoring assessments.

Pre-treatment differences between the conditions will be investigated using *χ*^*2*^ tests for categorical variables and ANOVAs for continuous variables. Linear mixed model analyses will be used to investigate the effectiveness and maintenance effects of Featback. Time contrasts will be created by means of dummy-coding. Within- and between-group effect sizes (Cohen’s *d*) [48] will be calculated based on the pooled standard deviation. As recommended by Frazier, Tix and Barron [49], potential categorical predictor or moderator variables will be dummy coded, and potential continuous predictor or moderator variables will be standardized. A significant two-way interaction between predictor and time indicates a predictor effect. A significant three-way interaction between time, condition and moderator, indicates a moderator effect. Significant moderator effects of continuous variables will be interpreted by dichotomizing the moderator variable into subgroups of participants who score either low or high (e.g., below or above the sample mean) on the moderator variable. Separate mixed model analyses will then be repeated to examine interactions between condition and time within the low and high subgroups.

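### The 25% sample size cut assumes adjustment for T0, but the mixed model described does not specify it and, on its most natural reading, loses most or all of the gain

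*Protocol article*

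**What the plan says.** The Sample size section of the protocol article defines the primary hypothesis as a comparison of levels after the intervention, namely: "average post-intervention level of eating pathology in the waiting list control condition is higher than the average level of eating pathology" among participants given any of the three forms of Featback. The design assumption is d = 0.32, and the calculation is framed as follows: "Assuming an alpha of 0.05 and a power of 0.80 (β-1) in a one-way ANOVA study". From this it concludes "we need sample sizes of 79 participants in each of the four groups whose means are to be compared using a planned comparison". It then assumes a correlation of 0.5 between T0 and the outcome, "thus explaining 25% of the variance of the outcome variable, the sample size per group can be reduced by 25" per cent. That gives 60 per group, then 86 after 30% dropout, and 344 in total.

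The Statistical analyses section names linear mixed models for effectiveness and maintenance. On the structure of the model it says "Time contrasts will be created by means of dummy-coding". A predictor effect is defined as predictor by time, and a moderator effect as time by condition by moderator. After a significant continuous moderator, mixed models are to be run again to "examine interactions between condition and time within the low and high subgroups". No T0 covariate is named for the effectiveness model. No reference level for time is given, nor any constraint on T0 means. The section sets a two-tailed level: "significance level of *α* = 0.05 will be used throughout the analyses".

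**The concern.** The factor 0.75 belongs to a particular analysis: one that adjusts the post-intervention score for T0, or treats the randomised arms as sharing one T0 mean. The analysis section reads as a different model, in which T0 is one of the repeated outcomes and effects are differences between arms in change from T0. That model does not have variance factor 1 − r². If it is the one fitted, the sample size has taken credit for precision that the analysis does not deliver, although the T0 scores needed to obtain it are already scheduled for every participant (Table 1). The Trial status section says enrolment is complete, so the choice of model is the practical way left to recover that precision.

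**Working it through.** **Inputs.** From the Sample size section: d = 0.32, alpha 0.05, power 0.80, 79 per group before adjustment, r = 0.5, 60 evaluable and 86 recruited per group. From Statistical analyses: two-tailed testing. The outcome SD is set to 1, and equal variances at T0 and T1 are assumed.

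**Reproducing the plan's figures.** The contrast of the waiting list with the mean of three equal active arms has variance (1 + 1/3)/n = (4/3)/n.

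- One-sided 0.05: n = (4/3)(1.645 + 0.842)²/0.32² = 80.5, so 81. This is close to the stated 79.
- Two-sided 0.05: n = (4/3)(1.960 + 0.842)²/0.32² = 102.2, so 103. This does not reproduce 79.
- Later steps: 0.75 × 79 = 59.25, so 60; 60 × 10/7 = 85.7, so 86; 4 × 86 = 344. All agree.

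**Variance of the T1 contrast at r = 0.5.**

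- *T0 as covariate, or T0 means constrained equal:* (4/3)(1 − r²)/60 = (4/3)(0.75)/60 = 0.01667.
- *T0 as a free outcome, condition by (T1 versus T0), 60 complete pairs:* (4/3) × 2(1 − r)/60 = (4/3)(1.00)/60 = 0.02222. Ratio 0.02222/0.01667 = 1.33.
- *T0 as a free outcome, 86 baselines and 60 T1 values per arm:* (4/3)[(1 − r²)/60 + (1 − r)²/86] = (4/3)(0.75/60 + 0.25/86) = 0.02054. Ratio 0.02054/0.01667 = 1.23.

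Reading the T1 level rather than the change from a free-baseline model does not help. With complete pairs its factor is also 1.00. With 86 baselines its variance is (4/3)[(1 − r²)/60 + r²/86], which at r = 0.5 is again 0.02054.

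A generalised least squares check with all four time points, and no T3 in the waiting list arm, gave factors of 1.00 (free baseline, complete data) and 0.75 (constrained). This held under both compound-symmetric and first-order autoregressive correlation.

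**Power at d = 0.32** (normal approximation, Φ(0.32/√variance − z)):

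| Model | Variance | 0.32/√variance | One-sided 0.05 | Two-sided 0.05 |
|---|---|---|---|---|
| T0 covariate or constrained | 0.01667 | 2.479 | 80% | 70% |
| Free T0, 86 baselines | 0.02054 | 2.233 | 72% | 61% |
| Free T0, 60 pairs | 0.02222 | 2.147 | 69% | 57% |

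The drop from 80% to 70% along the first row is the separate question of one-sided against two-sided testing. The loss from the handling of T0 is the drop down each column.

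**Dependence on r** (complete pairs). The change factor is 2(1 − r); the covariate factor is 1 − r².

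| r | 2(1 − r) | 1 − r² |
|---|---|---|
| 0.3 | 1.40 | 0.91 |
| 0.4 | 1.20 | 0.84 |
| 0.5 | 1.00 | 0.75 |
| 0.6 | 0.80 | 0.64 |
| 0.7 | 0.60 | 0.51 |

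The change contrast meets the planned 0.75 when 2(1 − r) ≤ 0.75, that is r ≥ 0.625.

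**Sample size if the free-baseline model is kept at r = 0.5.** On complete pairs there is no reduction: 79/0.7 = 112.9, so 113 per group and 452 in total, against 344. If all recruited baselines are used, with 70% of participants observed at T1, the factor is 0.75 + 0.25 × 0.70 = 0.925. Then 0.925 × 79 = 73.1, so 74; 74/0.7 = 105.7, so 106 per group and 424 in total. Both totals take the plan's 79 as given.

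**The case against.** The strongest reply is that no sentence puts T0 in the outcome vector. Dummy-coded time fits a model of T1 to T3 with T0 as covariate equally well. The condition by time wording appears only in the follow-up of moderators. The Sample size section itself describes the primary analysis as a post-intervention level that takes a baseline variable into account, which matches 0.75. How baseline enters a mixed model is also a detail that a protocol article may leave to a fuller document.

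Part of this stands. A reader might infer that the two sections flatly contradict each other, and the text does not support that. T0 as a free outcome is an inference, and a covariate or constrained-baseline model can be fitted within the words used.

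The inference is nonetheless the more natural one. Under the section's own definitions, a predictor acts through predictor by time and a moderator through time by condition by moderator. If time covered only T1 to T3, those terms would describe change during follow-up, not response to an eight-week intervention. The instruction to run the mixed models again for condition by time in subgroups also suggests that the main model contains that term. And this is more than a missing detail: the article publishes a sample size that depends on one specific adjustment, then describes effect tests that do not mention it.

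Two further readings go too far. One is that the gain from baseline is wholly lost. That holds for complete pairs at r = 0.5, but an intent-to-treat mixed model using all 86 baselines recovers about 8% of the variance (0.02054 against 0.02222). The other is that the handling of T0 alone brings power from 80% down to 57%. That figure also contains the one-sided against two-sided shortfall.

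**Conclusion.** The concern holds in a limited form. The analysis section does not specify the baseline adjustment on which the cut from 79 to 60 relies, and under its most natural reading that cut is not earned. At the plan's r = 0.5, the excess variance of the primary contrast is 23% to 33%, depending on whether baselines of participants without T1 contribute. The power cost attributable to this alone is about 8 to 11 points on the one-sided basis (80% to 69–72%) and about 9 to 13 points at the stated two-tailed level (70% to 57–61%).

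These figures assume equal variances at T0 and T1, 60 evaluable participants per arm, and T0 as a free outcome level. If T0 is in fact a covariate, or its means are constrained equal, there is no loss and the steps from 79 to 344 stand. If the true correlation is 0.625 or more, even the complete-pairs change contrast meets the planned factor.

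**What to change.** In Statistical analyses, state the primary effectiveness model in one of two forms:

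- T0, T1, T2 and T3 as outcomes with T0 means constrained equal across the four randomised arms: no condition main effect, and condition by time terms at T1 to T3 (waiting list to T2 only).
- T1 to T3 as outcomes with the T0 score as covariate.

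In either case, name the waiting list versus the mean of the three active arms at T1 as the primary contrast. The constrained form keeps every randomised participant with a T0 score in the analysis, which suits the protocol's intent-to-treat definition. The cost is one line of model specification, with no new data or participants. If the free-baseline model is kept, withdraw the 25% reduction in the Sample size section and restate the power for the numbers recruited.

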The following variables will be tested as potential predictors or moderators of intervention response: demographic variables (age, gender, educational level), motivation to change (importance, ability and readiness to change), severity of ED symptoms (SEED, EDE-Q) [23,37], severity of symptoms of depression and anxiety (PHQ-4) [31], early working alliance (SRS) [38], and compliance.

Mediator variables and their corresponding dependent variable will be measured frequently throughout this study, at T0 and T1, as well as once every two weeks in between T0 and T1. The variables repetitive negative thinking (PTQ) [32] and symptoms of depression and anxiety (PHQ-4) [31] will be tested as mediators of intervention outcome, being symptoms of ED as measured by the SEED [23].

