### Session rating scale (SRS)

The SRS [38] will be used to measure the working alliance between participants and their coaches, as well as to measure the perceived degree of support from the automated feedback messages and coaches, respectively. The SRS consists of four items that assess four aspects of the working alliance: the relational bond, the degree to which desired goals and topics of the individual are discussed, an evaluation of the therapist’s approach or method used, and an evaluation of the overall perception of the session by the individual. Instead of using a visual analogue scale, an 11-point Likert scale will be used to answer each of the four items, with ‘0’ depicting a negative response and ‘10’ depicting a positive response. The SRS demonstrated a high test-retest and internal consistency reliability, as well as an acceptable validity [38].

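### Baseline SEED or EDE-Q by time cannot show a predictor effect on the same measure, and SRS and compliance cannot act as moderators across the four conditions

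*Protocol article*

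**What the plan says.** Under Assessments, the protocol article names SEED and EDE-Q as the primary outcome measures. The same section then lists variables to be tested as potential predictors or moderators, without giving each one a role. The list includes "severity of ED symptoms (SEED, EDE-Q") and "early working alliance (SRS) [38], and compliance".

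Statistical analyses sets two rules. For predictors: "A significant two-way interaction between predictor and time indicates a predictor effect". For moderators, a significant interaction of time, condition and the candidate variable is taken as moderation. A significant continuous moderator is followed up by looking at condition by time within low and high subgroups. Time is dummy-coded. The section does not say whether T0 is a response level or a covariate.

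On the two process variables:
- Compliance is a count of completed weekly monitoring assessments (section Compliance).
- The SRS is asked after the first week of participation (Table 1, note 1). It covers the alliance with the coach and the "perceived degree of support from the automated feedback messages and coaches, respectively" (section Session rating scale).
- The waiting list is offered the intervention only after T2 (section on the waiting list control condition), and Ethical precautions and crisis management refers only to screening data for that arm.

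**The concern.** The second aim is to learn when or for whom the intervention works. Two parts of the stated rules do not serve it.

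First, when the predictor is the T0 score of the outcome itself, predictor by time restates how far people with high scores fall back towards the mean. That happens in any arm, treated or not. A rule that fires whether or not severity matters carries no information, yet its output would be reported as more severe participants improving most.

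Second, a moderator has to be defined in every condition compared and must not be a product of the condition. SRS and compliance meet neither requirement. A reported moderator effect for them would look like a finding about who benefits, but would be an association between taking part and doing well.

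**Working it through.** **Inputs, all from the protocol article.** Two-tailed alpha 0.05 (Statistical analyses). From Sample size: d = 0.32, baseline–outcome correlation r = 0.5, 79 per group reduced to 60, 30% dropout, 86 per group, 344 in total.

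**The plan's own figures.**
- 0.75 × 79 = 59.25, stated as 60. Then 10/7 × 60 = 85.7, so 86, and 4 × 86 = 344. Evaluable: 4 × 60 = 240.
- The 79 itself, for the waiting list against the mean of three active arms, is (4/3) × ((z_alpha + z_power)/0.32)². One-sided this gives 80.5, so 81, close to 79. Two-sided it gives 102.2, so 103. That mismatch with the two-tailed level is a separate matter; only the 240 is used here.

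**Is T0 a time level?** If T0 were only a covariate, the effect at T1 would be a main effect of condition, and condition by time would show only what changes after T1. Reading intervention response from condition by time, and moderation from the three-way term, makes sense only if T0 is a level of time.

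**Own baseline by time, no true predictor effect.** With equal variances:
- slope of (T1 − T0) on T0 = r − 1
- correlation of change with T0 = (r − 1)/√(2(1 − r)) = −√((1 − r)/2)
- t = corr × √(N − 2)/√(1 − corr²)

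At r = 0.5, N = 240: slope −0.5 SD, correlation −0.50, t = −0.5 × √(238/0.75) = −8.9.

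| r | slope (SD) | correlation | abs. t | P(significant) |
|---|---|---|---|---|
| 0.5 | −0.50 | −0.50 | 8.9 | 1.00 |
| 0.7 | −0.30 | −0.39 | 6.5 | 1.00 |
| 0.8 | −0.20 | −0.32 | 5.1 | 1.00 |
| 0.9 | −0.10 | −0.22 | 3.5 | 0.94 |
| 0.95 | −0.05 | −0.16 | 2.5 | 0.70 |

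The slope vanishes only if r × SD at T1 equals SD at T0. At r = 0.5 the SD would have to double.

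**Simulation.** 4,000 trials per setting, 60 per arm, a constant effect of 0.32 in each active arm, and no predictor or moderator effect, at r = 0.5 / 0.7 / 0.9:
- own baseline by time: rejected in 100% / 100% / 94%
- time by condition by baseline severity: 4.7% / 5.7% / 5.4%, which is nominal
- own baseline by time over post-baseline visits only: 5.1% / 4.6% / 5.0%

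**One instrument predicting the other (SEED to EDE-Q or the reverse).** The predictor rule rejects in about 5% if the T0 errors are independent. With an assumed error correlation of 0.3 it rejects in 65% (r = 0.5) or 44% (r = 0.7). The article gives no figure for that correlation.

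**SRS and compliance.**
- Both are recorded after randomisation, during the intervention.
- The waiting list has no monitoring, feedback or coach before T2, and no T3 assessment afterwards. A four-arm model of condition by compliance, with the waiting list at zero, has rank 7 of 8, so the slope in that arm cannot be estimated.
- The basic condition has no coach, so its SRS can rate only automated messages, while the supported arms also rate a coach. The score does not mean the same thing across even the active arms.

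**The case against.** **T0's place in the model is not stated.** The Sample size section treats T0 as a covariate, and with T0 out of the response the artefact disappears (4.6% to 5.1% above). This is fair: the finding depends on T0 being a time level. But the article's own rules for intervention response need that model.

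**The moderator rule.** A reader might infer that baseline severity as a moderator is contaminated too. It is not: regression to the mean is the same in all randomised arms and cancels, as the near-5% rejection rates show. This is also the test that speaks most directly to who benefits.

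**Other predictors.** A reader might infer that anything correlated with baseline severity, such as PHQ-4, inherits the artefact. For a predictor correlated 0.2, 0.3 or 0.5 with T0, simulated rejection is about 33%, 64% and 97%, but only if the predictor is tied to the observed T0 score, transient noise included. If it is tied to the stable true score, rejection is about 5% throughout. The article does not say which holds, and for age, gender or education the second is at least as natural.

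**A T0-adjusted outcome for every predictor.** This is tempting, but it is Lord's paradox, not a correction. For a predictor tied to the stable score at r = 0.5, the partial correlation with T1 given T0 is (0.2 − 0.2 × 0.5)/√(0.96 × 0.75) = 0.118, or 0.182 starting from 0.3. At N = 240 the adjusted test then rejects in about 45% and 81%, against 5% under the plan's rule.

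**SRS and compliance.** No passage says that the waiting list will be included for them or that a causal reading is intended. Within the active arms, with no link to outcome, compliance by time rejects in 4.9%. Other rates need added assumptions: 46% if the waiting list is coded zero and pooled without condition, and nearly 100% if improvement drives compliance (assumed log-odds 0.3 per SD). These rates show what could go wrong, not what is planned. What stands is that both variables are on the list to which the three-way rule applies, with no restriction to arms where they exist.

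**Conclusion.** The point holds in two parts.

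The predictor rule is uninformative when the predictor is the baseline value of the same outcome. At the plan's r = 0.5 and 240 evaluable it is significant in practically every trial without a true predictor effect, and in about 94% at r = 0.9. This assumes T0 as a time level and variances that do not grow enough to offset the slope.

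The three-way moderator rule cannot be applied to SRS and compliance across the four conditions, and a significant result would not be moderation. That neither exists in the waiting list is inferred from the descriptions of the conditions; the Table 1 note excluding that arm is not attached to the monitoring or SRS rows.

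The documents do not support extending this to the moderator test for baseline severity, to the other baseline predictors, or to a claim that the plan will read compliance causally. It concerns the second aim; the primary comparison is unaffected.

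**What to change.** 1. State that own-baseline severity by time will not be interpreted as a predictor effect, and test baseline SEED and EDE-Q only through their interaction with condition. This also settles the case of one instrument predicting the other.
2. Take SRS and compliance off the moderator list. Report them only as associations within the active arms, labelled non-causal, and note that the SRS rates different things in the basic and supported arms.
3. Leave the rule for the other baseline predictors as it is.

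The cost is wording only, since every variable is already collected. The price is that two variables leave the moderator list and own-baseline severity is no longer reported as a non-specific predictor.

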#### Assessments

All assessments are self-reported and will be conducted online. Table 1 depicts an overview of the assessment instruments that will be used throughout each stage of the study. Primary outcome measures are disordered eating behaviors and attitudes (SEED, EDE-Q) [23,27]. Secondary outcome measures contain ED-related quality of life (ED-QOL) [28], self-stigma of seeking help [29], self-esteem, mastery and support [30], symptoms of depression and anxiety (PHQ-4) [31], repetitive negative thinking (PTQ) [32], motivation to change [33,34], and user satisfaction, as well as compliance and help-seeking attitudes and behaviors. Cost-effectiveness will be evaluated by means of the reported quality of life (EQ-5D) [35] and medical and societal costs (Trimbos/iMTA Questionnaire for Costs Associated with Psychiatric Illness: TiC-P) [36].

**Table 1 T1:** Overview of the assessment instruments used throughout each stage of the study

**Assessment**	**Screening**	**T0: Baseline**	**Weekly monitoring: even weeks**	**Weekly monitoring: uneven weeks**	**T1: Post-intervention**	**T2: 3-month follow-up**	**T3: 6-month follow-up**^2^
Weight Concern Scale (WCS)	X	-	-	-	-	-	-
Short Evaluation of Eating Disorders (SEED)	X	X	-	-	X	X	X
Short Evaluation of Eating Disorders II (SEED-II)	-	-	X	X	-	-	-
Demographics and other information	-	X	-	-	-	-	-
Monitoring questionnaire	-	-	X	X	-	-	-
Patient Health Questionnaire 4 (PHQ-4)	-	X	-	X	X	X	X
Perseverative Thinking Questionnaire (PTQ)	-	X	-	X	X	X	X
Eating Disorder Examination Questionnaire (EDE-Q)	-	X	-	-	X	X	X
Self-stigma of seeking help	-	X	-	-	X	X	X
Self-esteem, mastery and support	-	X	-	-	X	X	X
Eating Disorder-related Quality of Life (ED-QOL)		X	-	-	X	X	X
Motivation to change	-	X	-	-	X	X	X
Session Rating Scale (SRS)	-	-	X^1^	-	-	-	-
User satisfaction questionnaire	-	-	-	-	X^2^	-	-
Attrition follow-up question	-	-	X^3^	X^3^	X^3^	X^3^	X^3^
Help-seeking attitudes and behavior questionnaire	-	-	-	-	X	X	X
Quality of life (EuroQol: EQ-5D)	-	X	-	-	X	X	X
Trimbos/iMTA questionnaire for costs associated with psychiatric illness	-	X	-	-	X	X	X

^1^Only asked after participants’ first week of participation.

^2^Not sent to participants who are randomized to the waiting list control condition.

^3^Sent to participants who fail to complete the monitoring assessment, or the T1, T2 or T3 assessment, respectively.

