### Short Evaluation of Eating Disorders (SEED)

The SEED [23] is a brief self-report measure for the assessment of key ED symptoms. It assesses the three main symptoms of anorexia nervosa (degree of underweight, fear of weight gain, and distortion of body perception) and bulimia nervosa (amount of binge eating, amount of compensatory behavior, and over concern with body shape and weight). Total severity indexes can be calculated for each of the two diagnoses (range 0–3), with higher scores reflecting higher severity indexes. The behavioral measures (bingeing, excessive exercising, and compensatory behaviors) are assessed over the previous four weeks. The SEED has demonstrated construct validity and criterion-related validity, and was furthermore shown to be sensitive to symptom change [23].

Given that the SEED will be administered every week during the intervention period as well, the four-week timeframe for the behavioral measures is adapted to a timeframe of one week. This adapted questionnaire will be referred to as SEED-II.

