### Compliance

Two measures of compliance will be extracted from the database. The first measure of compliance will be the number of times a participant has completed the weekly monitoring assessment. The second measure of compliance will be the number of times a participant has completed a monitoring assessment after a completed assessment in the previous week. This second measure of compliance is important because Featback is only programmed to compare obtained results with those of the previous week, not with those completed at earlier points in time. Thus, in case one has missed a monitoring assessment, but completes the next monitoring assessment a week later, results of the completed assessment cannot be compared to the previous results (e.g., results of the previous week are missing). Subsequently, progress or deterioration cannot be accurately monitored, which in turn can produce more general and less individually tailored feedback. To be able to further investigate dose–response relationships, the number of support sessions a participant has received will be recorded as well.

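### Any three-way interaction with p < 0.05 is read as a moderator, with no correction or exploratory label over 9 to 11 candidates, so false moderators are far likelier than 5%

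*Protocol article*

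**What the plan says.** The rule is in the Statistical analyses section of the protocol article: "A significant three-way interaction between time, condition and moderator, indicates a moderator effect". A parallel sentence says the same of predictor-by-time interactions and predictors. The level is set once for everything: "A two-tailed significance level of *α* = 0.05 will be used throughout the analyses". For a continuous moderator, a significant result leads to a split into low and high groups, for example at the sample mean, and separate mixed models within each group.

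The candidates are in the Assessments section: "demographic variables (age, gender, educational level), motivation to change (importance, ability and readiness to change), severity of ED symptoms (SEED, EDE-Q" and then "severity of symptoms of depression and anxiety (PHQ-4) [31], early working alliance (SRS) [38], and compliance". The Compliance section adds that "Two measures of compliance will be extracted from the database".

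On outcomes, the Assessments section says "Primary outcome measures are disordered eating behaviors and attitudes (SEED, EDE-Q", and the SEED section says "Total severity indexes can be calculated for each of the two diagnoses (range 0–3". The article does not say which of these scores stands for intervention response in the moderator analysis. The Background makes predictors, moderators and mediators the second aim of the study, after effectiveness.

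**The concern.** Read as written, the two sentences form a decision rule: each candidate is tested at 0.05 and each significant test yields a moderator. Over many tests, the chance that at least one is significant by accident is well above 5%. Nothing in the article corrects for this or marks the results as exploratory.

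A chance hit on a continuous variable would start the low/high subgroup models and could be reported as a finding about who benefits from Featback. The program is presented as one whose components can be matched to the participant, so such a finding could influence who is offered coach support.

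**Working it through.** **The plan's own figure.** There is none to reproduce. The article gives neither a number of moderator tests nor an error rate for the family.

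**Candidates (Assessments).** Age, gender, education, three motivation items, SEED, EDE-Q and PHQ-4 make 9. Splitting SEED into its two indexes makes 10. Counting by name with working alliance and compliance added to the 9 makes 11. Splitting both SEED and compliance makes 13. The main figures use 9–10. Working alliance and compliance depend on using the program and have no counterpart on the waiting list.

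**Scores.** One score is possible. Two are possible if SEED and EDE-Q each give one. Three follow from EDE-Q global plus two SEED indexes. The choice is an assumption in every case.

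**Independent tests, no true moderation.** P(at least one p < 0.05) = 1 − 0.95^k, and the expected number of false hits is 0.05k.

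- k = 9: 1 − 0.95^9 = 37.0%; expected 0.45
- k = 10: 1 − 0.95^10 = 40.1%; expected 0.5
- k = 20: 1 − 0.95^20 = 64.2%; expected 1.0
- k = 30: 1 − 0.95^30 = 78.5%; expected 1.5

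**Correlated tests.** Scores and candidates are correlated, which lowers the chance of at least one hit but leaves the expected number unchanged. This was simulated with no effects: four arms of 60 or 86, change scores, one 3-df condition-by-moderator F test per pair, and 1,500 runs per case (Monte Carlo error about 1 percentage point). The correlations are assumed: 0.5–0.7 between scores and 0.3–0.5 between candidates.

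| Scores | Tests | Correlated | Independent | Range |
|---|---|---|---|---|
| One | 9–10 | 32–37% (candidates correlated 0.3–0.4) | 37–41% | about 32–41% |
| Two | 20 | 44–55% | 64% | about 44–64% |
| Three | 30 | 54–70% | 79% | about 54–79% |

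The 41% is the simulated value for 10 independent tests; the exact value is 40.1%.

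**Larger counts.** With three scores, 11 candidates give 33 tests: 81.6% if independent and 58–73% if correlated. Thirteen candidates give 39 tests: 86.5% and 62–76%. If each dummy-coded arm contrast is read separately, in place of one omnibus test, the 10 × 3 case gives 86–99%. The completers analysis, the follow-up time contrasts and the predictor-by-time tests are not counted in any of these figures.

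**With a correction.** Bonferroni over 30 independent tests, at 0.05/30 = 0.00167 each, gives 1 − (1 − 0.00167)^30 = 4.9%. When no moderator is real, every declared one is false, so Benjamini-Hochberg at 5% also holds the chance of any declaration to 5% for independent tests.

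**The case against.** Several parts of the opposing case stand.

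- **The number of tests is not in the document.** A reader might infer that the plan commits to about 30 tests and so produces a false moderator more often than not. The text does not support that. The mediation analysis names only the SEED as its outcome, the sample size section speaks of one level of eating pathology, and the candidates are called predictors or moderators without saying that each gets both tests. With one score the chance stays below one half.
- **A single hit is not worthless.** A reader might infer that one significant moderator carries almost no information. That does not follow from a family-wise rate, which describes the chance of any hit. With 240 completers (4 × 60) and an assumed interaction of f² = 0.02–0.03, power at 0.05 is 42–60%. A significant result is then 42/5 to 60/5, or about 8 to 12 times, likelier under such an effect than under none.
- **Correction costs power.** At 0.05/30 that power falls to 8–17%. A compulsory family-wise correction for a secondary aim is a debatable trade.
- **The framing is partly cautious.** The aims speak of potential variables and of gaining insight, no directional moderator hypothesis is stated, and the study is powered only for the main comparison. Requiring the interaction before any subgroup model is itself a safeguard.

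Two arguments stand only in part. A common level of 0.05 does not forbid a correction run at 0.05, and an unseen analysis plan may contain one. But this article itself states what a significant interaction is taken to show, without qualification. The rule may also be read as only naming the model term that represents moderation, yet it is the sole criterion given and it leads directly to the subgroup models.

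**Conclusion.** The concern holds in limited form. As written, the rule gives a chance of at least one false moderator far above the nominal 5% on every reading of the test count examined: at the low end of the ranges 32/5, or more than six times. Which range applies depends on how many scores are tested, which the article leaves open, and on assumed correlations. The calculation also assumes one omnibus test per candidate and score at a single time contrast, with no true moderation anywhere.

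Severity is minor. The comparison of the active conditions with the waiting list is untouched. What changes is what the trial may conclude under its second aim.

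**What to change.** In the Statistical analyses section:

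1. List the moderator tests to be run on the primary scores, naming the scores and candidates, so that the number of tests is fixed.
2. Use one omnibus condition-by-time-by-moderator test for each candidate and score.
3. Declare a moderator only if its test survives a Benjamini-Hochberg correction at 5% over that list. This is compatible with the common 0.05 level.
4. Report all other interactions with p < 0.05, and any low/high subgroup models based on them, as hypothesis-generating, with estimates, confidence intervals and the number of tests.
5. Treat the predictor-by-time tests in the same way.

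This is a change of wording and needs no new data, so completed enrollment is no obstacle. The cost is lower power to declare a single moderator. If only one effect is real and it shows on only one score, Benjamini-Hochberg is nearly as strict as Bonferroni; it gains when several are real. No estimate is lost, because every interaction is still reported.
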